#### *Data collection*

After we have received informed consent from the parents/guardians, blood samples from the infant will be taken according to present clinical practice. If possible 2ml cord blood and 0.6 ml blood at days 0, 72h, 7, 14 and from that time point every second week until postmenstrual week 29, and thereafter at 30, 32, 34, 36 and 40 weeks postmenstrual age will be taken.

Breast milk samples will be taken day 7 and at PMA of 32 and 40 weeks. Length, weight and head circumference are measured weekly.

Screening for ROP will be performed, at least once a week, according to clinical routines using a specific protocol.

We intend to analyze the content of phospholipids which can be done on small amounts of blood, is relatively insensitive to short term fluctuations in intake and mirror the composition of many membranes in the body. The analyses will be made using gas-liquid chromatography. The method has a coefficient of variability of 1-3% for the fatty acids concerned.

47

**Mega Donna Mega Site:****Schedule****Study nr:** \_\_\_\_\_

|                                                                                                                                                                             | d
a
y
0 | d
a
y
1 | d
a
y
2 | ho
ur
7
2 | d
a
y
4 | d
a
y
5 | d
a
y
6 | d
a
y
7 | d
a
y
1
4 | W
3              | W
4 | W
5 | W
6 | w
7 | P
M
A
30+0
+-
24h | P
M
A
31+0
+-
24h | P
M
A
32+0
+-
24h | P
M
A
33+0
+-
24h | P
M
A
34+0
+-
24h | P
M
A
35+0
+-
24h | P
M
A
36+0
+-
24h | P
M
A
37+0
+-
24h | P
M
A
38+0
+-
24h | P
M
A
39+0
+-
24h | P
M
A
40+0
+-
24h |

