| Registration of HR+MABP every second hour
up to day 7 (excel)                                                                                                            | x                | x                | x                | x                  | x                | x                | x                | x                |                       |                     |        |        |        |        |                                  |                                  |                                  |                                  |                                  |                                  |                                  |                                  |                                  |                                  |                                  |
| Study sample cord blood (2 ml). 0h, 72h,
d7, d14 (+/- 6 h) every other week until PMA 29w
and thereafter at 30, 32, 34, 36, and 40 weeks PMA
(0,6 ml), (+/- 24 h). | x                |                  |                  | X                  |                  |                  |                  | x                | x                     |                     | x      |        | x      |        | x                                |                                  | x                                |                                  | x                                |                                  |                                  |                                  |                                  |                                  | x                                |
| Blood gas                                                                                                                                                                   | x                |                  |                  |                    |                  |                  |                  |                  |                       |                     |        |        |        |        |                                  |                                  |                                  |                                  |                                  |                                  |                                  |                                  |                                  |                                  |                                  |

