### 7.3 Informed Consent/Assent Form

Informed consent by the parents/guardians for each subject will be obtained before initiating any study procedures. Both parents/guardians will have to sign the informed consent. Informed consent should be obtained as soon as possible after birth and no later than 36 hours after birth. One copy of the signed and personally dated informed consent must be given to each parent/guardian and one signed and personally dated copy must be retained in the investigator's trial records. The “Declaration of Helsinki” recommends that consent be obtained from each potential subject or parents/guardians in biomedical research trials after the physician has explained to the individual the purpose, methods, anticipated benefits, and potential hazards of the trial and discomfort it may entail.

Potential subject's parents/guardians should also be informed of their right not to participate or to withdraw from the study at any time. If the individual is in a dependent

relationship to the physician or gives consent under duress, an independent physician should obtain the informed consent. If the individual is legally incompetent (i.e., a minor or mentally incompetent), informed consent must be obtained from the parents, legal guardians, or legal representative in accordance with the law in Sweden. See the “Declaration of Helsinki”.

If a protocol amendment substantially alters the study design or there is an increase of a potential risk to the subject:

- the informed consent form or subject information sheet must be revised and submitted to EPN for review and approval; and
- the approved revised form must be signed by parents/guardians to subject currently enrolled in the study; or
- the new form must be used to obtain consent from new parents/guardians prior to enrollment into the study.

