### 3.2.2 Secondary Efficacy Variables

Following secondary efficacy variables will be analysed:

- Postnatal serum fatty acid (in mol%) composition in preterm infants with and without AA:DHA supplementation (at 0h, 72h, day 7, day 14, every second week until PMA of 29 weeks and thereafter at 30, 32, 34, 36, 40 weeks PMA). Missing data will not be imputed, analysis will be performed using Mixed Models for Repeated Measures (MMRM) where missing data at random is assumed.
- Outcome of neonatal morbidities (reported as Adverse Events [AE] from birth to 40 weeks PMA)
  - BPD – this morbidity is evaluated at 36 weeks PMA and will be analysed including the complete ITT population with deaths considered as non-events but their follow-up time will contribute to the total follow-up in the analyses of event rate performed by Poisson regression. Sensitivity analysis of BPD will be performed handling all deaths as endpoint also beside confirmed BPD. Drop-out due to other reasons will be considered as non-event.
  - IVH grade 0-4 – this morbidity is evaluated at an early stage post-birth, and larger amount of missing data is not expected. Drop-outs with missing IVH will be handled as non-events. Sensitivity analysis of IVH will be performed handling all deaths with missing IVH as worst value of this endpoint (?). Drop-out due to other reasons will be considered as non-event. Analyses will be performed using Mantel-Haenszel Chi-square test.
  - PDA - this morbidity is evaluated at an early stage post-birth, and larger amount of missing data is not expected. Drop-outs with missing PDA will be handled as non-events. Sensitivity analysis of PDA will be performed handling all deaths with missing PDA as event (?). Drop-out due to other

|                                     |  |                                    |               |
|-------------------------------------|--|------------------------------------|---------------|
| STATISTISKA KONSULTGRUPPEN   |  | Statistical Analysis Plan          |               |
| Protocol:
Mega Donna Mega |  | Protocol No:
MEGADONNAMEGA 16-7 |               |
|                                     |  | Version:
1.0                    | Page 14 of 21 |

reasons will be considered as non-event. Analyses will be performed using Fisher's Exact test.

- NEC – this morbidity will be analysed in the same way as the primary variable, using Poisson regression in the main and survival analysis in the sensitivity analysis.

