## 4 STATISTICAL METHODOLOGY

### 4.1 General Methodology

For continuous variables mean, Standard Deviation (SD), median, minimum and maximum will be presented, or median and Interquartile Range (IQR) as applicable, and for categorical variables number and percentage.

The baseline characteristics will be described; inferential statistics will be performed and interpreted descriptively only.

The confirmatory analyses will be only performed for:

1. Primary efficacy variable, impact of IP on severe ROP (comparison of event rates)
2. Secondary efficacy variable, impact of IP on overall levels of AA (mol%) continuously over time
3. Secondary efficacy variable, impact of IP on overall levels of DHA (mol%) continuously over time
4. Secondary efficacy variable, impact of IP on BPD (yes/no at PMA week 36, comparison of event rates)
5. Secondary efficacy variable, impact of IP on IVH (grade 0-4)

For those analyses the difference in the estimates and their 95% Confidence Intervals (CI) will be provided, and tests will be adjusted for multiplicity according to the fix sequential method as per the sequential order above. This methods allows for the significance mass of 0.05 to be inherited to the next variable in order and the testing is stopped when non-significance is achieved.

|                                     |  |                                    |               |
|-------------------------------------|--|------------------------------------|---------------|
| STATISTISKA KONSULTGRUPPEN          |  | Statistical Analysis Plan          |               |
| Protocol:
Mega Donna Mega |  | Protocol No:
MEGADONNAMEGA 16-7 |               |
|                                     |  | Version:
1.0                    | Page 17 of 21 |

Missing data will be handled according to the section 3.2.

All other analyses will be considered as exploratory, 95% CI will be provided for the difference between the groups and p-values will be given only for descriptive purpose.

All tests will be two-tailed and confirmed analyses will be conducted at 0.05 level applying fix sequential testing. All analyses will be performed using SAS software version 9.4 (SAS Institute Inc., Cary, NC, USA).

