#### 4.6.2 Secondary Efficacy Analyses

Confirmatory analyses of secondary variables:

1. The secondary efficacy analyses of fatty acid levels over time will be evaluated by applying MMRM with the change in level of fatty acids (AA and DHA respectively) from birth as dependent variable, and visit, treatment group as fixed effects, fatty acid at birth as fix adjustment variable, with repeated measures by visit applying the covariance pattern (compound symmetry, autoregressive, Toeplitz, unstructured, overall and applied by treatment group) that minimizes the Akaike's Information Criterion (AIC). From this model without an interaction term the overall effect of the IP will be retrieved, presented by adjusted means with 95% CI. The assumption of normally distributed residuals will be checked by reviewing the diagnostic plots. If not satisfactory the sandwich estimators for the standard errors (resulting in wider CIs) will be applied. Additional model for descriptive (exploratory) purpose will be performed including interaction term from which the impact of IP over time will be retrieved and presented graphically.
2. The secondary efficacy analysis of the impact of IP on BPD will be analyzed on ITT population including infants for which BPD was evaluated at 36 weeks PMA, deaths and other drop-outs will be handled as non-events. Poisson regression with log-link function, will be performed, resulting in RRs with 95% CI and associated p-value.
3. The secondary efficacy analysis of the impact of IP on IVH (grade 0-4) will be analyzed on ITT population using all infants that have evaluated IVH, missing data will be considered as non-events. Mantel-Haenszel Chi-square test will be performed.

Following secondary variables will be analyzed descriptively:

1. PDA will be analyzed using Fisher's Exact test. Proportion of patients with events and 95% CI will be provided.
2. NEC will be analyzed in the same way as the primary efficacy variable, applying Poisson regression. RR with 95% CI will be provided.
3. Growth development, by computing difference with 95% CI between treatment groups in BWSDS, BLSDS, HCSDS for studied time points, only on infants born GA $\geq$ 24 weeks. Individual growth curves will be created by GA week and sex, per treatment group and mean curve estimated per each subgroup of infants.

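### The confirmatory AA and DHA model drops every infant without a birth sample, and the plan has no fallback; the cost is precision and departure from the ITT set, not demonstrated bias

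*Combined protocol and SAP*

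**What the plan says.** SAP 4.6.2 specifies an "MMRM with the change in level of fatty acids (AA and DHA respectively) from birth as dependent variable", with visit and treatment group as fixed effects and "fatty acid at birth as fix adjustment variable". SAP 3.2.2 adds: "Missing data will not be imputed, analysis will be performed using Mixed Models for Repeated Measures (MMRM) where missing data at random is assumed". In the fixed sequence of SAP 4.1, the second test is described as "Secondary efficacy variable, impact of IP on overall levels of AA (mol%) continuously over time"; DHA is third, BPD fourth and IVH fifth. SAP 4.6.2 places the main analyses on the ITT population.

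On how the birth value arises, protocol 7.3 states: "Informed consent by the parents/guardians for each subject will be obtained before initiating any study procedures". It asks for consent as early as it can be had after birth, with an outer limit of 36 h. Protocol section 4 (Data collection) takes infant blood after consent and lists the samples thus: "If possible 2ml cord blood and 0.6 ml blood at days 0, 72h, 7, 14". The schedule table in that section prints a tolerance after the early time points: "d7, d14 (+/- 6 h) every other week until PMA 29w". Under protocol section 4, the online CRF gives the allocation once the parents have agreed.

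None of these places says whether *birth* means the cord sample or the 0 h/day 0 infant sample. None says what happens when the value is missing. The later clarification on the fatty acid analysis, appended to the SAP, only removes postnatal weeks 4 and 6 from the model.

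**The concern.** The missing-at-random argument for a mixed model covers post-birth visits that are missing from the response. It does not cover a missing covariate, or a response that cannot be computed because the value subtracted from it is missing. The stated handling therefore stops at the one sample on which every row of an infant's data depends.

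The procedures leave room for that sample to be absent. Consent comes after birth and before study blood, and the documents describe no way to obtain or hold cord blood while consent is awaited.

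Two things are at stake. First, the set analysed for two confirmatory tests would be the infants with a birth sample, not the ITT population that the SAP names. Second, precision is lost on tests that stand ahead of BPD and IVH, so a non-significant AA or DHA result would also end confirmatory testing of those two.

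**Working it through.** The plan gives no precision or power figure for AA or DHA, so there is no figure of its own to reproduce. Its sample size of 80 per group concerns any ROP and does not bear on this point.

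**Step 1: does the infant leave the model?** Write B for the birth value and Y(t) for the level at visit t. The response is Y(t) − B and B is also a covariate. If B is missing and nothing is imputed, every row of that infant is incomplete. Changing the response to Y(t) while keeping B as a covariate would not help, because B is still needed on each row.

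**Step 2: how many infants, and what loss of precision?** Inputs: 210 infants, 105 per arm (protocol 11.1). The share m without a birth value is not in the documents; 10%, 20% and 40% are assumed. If absence is unrelated to arm and outcome, the standard error (SE) rises by about 1/√(1 − m).

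| m (assumed) | Infants dropped, 210 × m | Infants left | SE factor 1/√(1 − m) |
|---|---|---|---|
| 10% | 21 | 189 | 1/√0.90 = 1.05 |
| 20% | 42 | 168 | 1/√0.80 = 1.12 |
| 40% | 84 | 126 | 1/√0.60 = 1.29 |

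To give these a scale, take a contrast that had 80% power at 105 per arm, two-sided 0.05. This is a hypothetical, since the plan powers nothing on AA or DHA. Power becomes Φ(2.80 × √(1 − m) − 1.96), which is about 76%, 71% and 58%.

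**Step 3: simulation check.** The set-up was 210 infants, 8 post-birth visits, between-infant SD 1, within-infant SD 0.7, true effect 0.50, birth values missing at random with respect to arm, and 60 runs per share. All these values are assumptions. The change-from-birth model with B as covariate and a random intercept gave:

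| Share missing | Mean infants used | Mean estimate | Mean SE | Ratio to complete |
|---|---|---|---|---|
| 0% | 210 | 0.50 | 0.0867 | 1.00 |
| 10% | 189 | 0.50 | 0.0907 | 1.05 |
| 20% | 169 | 0.50 | 0.0958 | 1.10 |
| 30% | 148 | 0.51 | 0.1031 | 1.19 |

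The model kept only infants with a birth value, the SE rose about as the formula predicts (1.20 at 30%), and the estimate stayed near the truth.

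**Step 4: how much can be recovered?** If the birth value is one of the repeated outcomes with a common mean, an infant without it still carries a fraction 1 − ρ² of the information of a complete infant. Here ρ is the correlation between the birth value and the post-birth mean. The SE factor becomes 1/√(1 − mρ²). With the variances of Step 3, the post-birth mean has variance 1 + 0.49/8 = 1.061 and the birth value 1.49, with covariance 1. So ρ² = 1/(1.061 × 1.49) = 0.63. The factors at 10%, 20% and 40% are then 1.03, 1.07 and 1.16, against 1.05, 1.12 and 1.29. The documents do not give ρ; a lower correlation means more is recovered.

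**The case against.** Three stronger readings are tempting, and the documents do not support them.

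- *That many birth samples will probably be missing.* No document counts them. The 36 h figure is an outer limit, consent is sought as early as it can be had, and protocol 6.2 expects the first dose within 24 h. The condition on sampling opens the list of all samples and does not single out the birth sample. Cord blood and the day 0 infant sample are two possible sources, and lacking one does not mean lacking both.
- *That an infant whose parents consent after 6 h has no birth value.* The tolerance in the schedule may cover the whole list of early samples or only the last one named. The table column is headed day 0, and nothing says that a sample outside the window is discarded.
- *That the treatment comparison is biased.* Consent timing is settled before the arm is known, so loss from that cause should be balanced. Staff giving the supplement are not blinded, so other causes of a missed sample could differ by arm, but nothing shows that they do.

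It can also be said that baseline-adjusted change is a standard and valid model. The supplement supplies AA and DHA directly, so the effect may be large enough for a modest SE increase not to matter. The two tests are confirmatory only if severe ROP is significant first. Some of the 210 infants would have no post-birth sample under any model, given the expected perinatal death rate of about 15%.

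All of this limits the size and certainty of the loss. It does not remove the exclusion rule built into the model, or the absence of a fallback.

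**Conclusion.** The point holds as one of precision and analysis population. As written, confirmatory tests 2 and 3 exclude any infant without a birth value, whatever later data exist, and neither the SAP nor its clarifications say what to do. That this will happen to some infants is foreseeable from the consent and sampling rules; how many is unknown.

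The SE increases of about 5%, 12% and 29% at assumed shares of 10%, 20% and 40% are approximate upper bounds. They compare with complete birth values, take all 210 infants as otherwise contributing, and assume absence unrelated to arm and outcome. The proposed model recovers part of the loss, not all of it. Because the documents give no effect size or variance for AA or DHA, the loss cannot be tied to a change in any conclusion. The change is worth making because it is cheap and uses data already planned.

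**What to change.** In SAP 4.6.2, model the AA and DHA levels with the birth value as the first of the repeated outcomes. Constrain the birth mean to be common to both arms, and include visit, one overall post-birth treatment effect, GA category and centre. Every infant with a post-birth sample then contributes to the treatment contrast. An infant with only a birth sample adds almost nothing to it. GA category and centre match the stratified randomization and the adjustment already used for the primary analysis in SAP 4.6.1; the present fatty acid model omits both. Modelling levels also fits the description of the test in SAP 4.1.

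In the same section:

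- Define which sample is the birth value (cord, or 0 h/day 0), its time window, and whether it must precede the first dose. The 36 h consent limit in protocol 7.3 and the 24 h start of supplementation in protocol 6.2 need to be reconciled for this definition to work.
- Report by arm the number of infants without a birth value.
- Keep the change-from-birth model as a sensitivity analysis.

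The cost is SAP wording and recoding one model, with slightly more modelling assumptions, namely a joint distribution for the birth and later values. No new data are needed, and clarifications to the SAP have already been issued by note-to-file.

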## 6 CHANGES OF ANALYSIS FROM PROTOCOL

No changes to protocol version 7b have been done. However, no detailed description of the analyses were available in the protocol. All analyses specified within this SAP are aimed to be conservative regarding the IP and applying ICH and EMA guidelines for statistical analyses and adjustments. Additionally, recently published guidelines from ASA and NEJM have been employed.

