### 3. Clarification on the analysis fatty acid secondary variable

**Original definition:** Postnatal serum fatty acid (in mol%) composition in preterm infants with and without AA:DHA supplementation (at 0h, 72h, day 7, day 14, every second week until PMA of 29 weeks and thereafter at 30, 32, 34, 36, 40 weeks PMA) will be analysed as secondary variable. Missing data will not be imputed, analysis will be performed using Mixed Models for Repeated Measures (MMRM) where missing data at random is assumed.

**Clarification:** Due to infants are born in different gestational weeks, serum fatty acid data for postnatal weeks 4 and 6 will be available only for a proportion of infants, those with the lowest gestational age at birth. Therefore postnatal weeks 4 and 6 will be only described but not used in planned MMRM analyses.

|                                     |                                    |               |  |
|-------------------------------------|------------------------------------|---------------|--|
| STATISTISKA KONSULTGRUPPEN          |                                    | Note-to-SAP 1 |  |
| Protocol:
Mega Donna Mega | Protocol No:
MEGADONNAMEGA 16-7 |               |  |
|                                     | Version:
1.0                    | Page 1 of 2   |  |

---

**SPONSOR:** [name]

**STUDY:** Mega Donna Mega

**TO:** SAP version 1.0 dated 19 November 2019

**DATE:** 14 April 2020

**SUBJECT:** Note-to-file to SAP - Clarifications

---

Following clarifications were not defined in detail in the final SAP and are documented in this note-to-file.

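### The sandwich fallback for the confirmatory AA and DHA models has the wrong trigger and does not generally widen intervals, and no small-sample correction is named

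*Combined protocol and SAP*

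**What the plan says.** SAP 4.6.2, confirmatory item 1, models change from birth in AA and in DHA, with visit, treatment and birth level as fixed effects. The covariance pattern is the one with the smallest AIC among "compound symmetry, autoregressive, Toeplitz, unstructured, overall and applied by treatment group". The tested quantity is the treatment main effect: "From this model without an interaction term the overall effect of the IP will be retrieved, presented by adjusted means with 95% CI".

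The safeguard comes next: "The assumption of normally distributed residuals will be checked by reviewing the diagnostic plots", and then "If not satisfactory the sandwich estimators for the standard errors (resulting in wider CIs) will be applied". The SAP gives no numerical rule for reading the plots, no degrees-of-freedom method and no small-sample correction for either kind of standard error.

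In SAP 4.1, AA and DHA are steps 2 and 3 of the confirmatory sequence: "All tests will be two-tailed and confirmed analyses will be conducted at 0.05 level applying fix sequential testing". SAP 6 adds: "All analyses specified within this SAP are aimed to be conservative regarding the IP". The later clarification on the fatty acid variable changed this same model ("Therefore postnatal weeks 4 and 6 will be only described but not used in planned MMRM analyses") and left the sandwich rule as it was.

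**The concern.** The rule ties a remedy to the wrong fault. The sandwich estimator keeps standard errors valid when the working covariance is wrong. It does nothing specific for skewed or heavy-tailed residuals: a treatment effect averaged over well over a hundred infants is close to normal anyway, and the sandwich relies on the same large-sample argument. A normality plot, in turn, is not designed to show a wrong covariance pattern. The safeguard can therefore stay off when it is needed and switch on when it brings nothing.

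Covariance doubt is real here because the visit spacing differs between infants. Day 14 falls at 24+0 weeks PMA for an infant born at 22+0 and at 29+6 for one born at 27+6. The gap to the 30-week sample thus runs from six weeks to one day, while an autoregressive or Toeplitz pattern indexed by visit order treats it as a single step for everyone.

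The remark on wider intervals presents the switch as the cautious choice, in line with the aim stated in SAP 6. If the switch usually narrows the interval, that description is wrong for two confirmatory tests, and a subjective reading of plots decides which standard error enters them.

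**Working it through.** **Inputs from the documents.** Randomised: 105 + 105 = 210 (SAP 1.3). Deaths: about 15% (SAP 1.4), leaving 210 x 0.85 = 178.5. Post-birth visits once weeks 4 and 6 are removed: 72 h, day 7, day 14 and PMA 30, 32, 34, 36, 40, so T = 8. Alpha: 0.05 two-sided. The SAP gives no figure for the sandwich step, so there is none to reproduce.

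**Assumptions.** Infants with usable data: 140-180 in total. A change from birth also needs a birth sample, so the number may fall below 178. Correlation structure, dropout and error distributions are also assumed.

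**1. Parameter count.** Unstructured covariance has T(T+1)/2 = 8 x 9/2 = 36 parameters, or 72 if fitted by arm.

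**2. What the switch does.** In simulated null trials with 180 infants and 18% dropout (t reference distribution; 1,500-2,500 trials per scenario, 800 for Toeplitz):

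| Pattern fitted | Median sandwich/model SE | Type I error, model-based | Type I error, sandwich |
|---|---|---|---|
| Compound symmetry | 0.991 | 4.5-5.1% | 4.6-5.2% |
| Toeplitz | 0.992 | 5.6% | 5.9% |
| Unstructured | 0.991 | 5.2-5.9% | 5.5-6.1% |
| AR(1), too simple for the simulated data | 1.12-1.18 | 8.0-9.2% | 4.6-5.1% |

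For the first three patterns the sandwich SE was the smaller one in about 82-93% of trials. The ratio alone moves alpha to 2 x [1 - Phi(1.96 x 0.991)] = 5.2%. Reaching 6% through the ratio alone would need 0.96, and 7% would need 0.92. The first was seen only with 40 infants in total; the second was not seen.

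**3. Is non-normality the right trigger?** With compound symmetry, model-based error was 4.5% for skewed and 4.8% for heavy-tailed errors. With unstructured covariance it was 5.6-5.8%, against 5.2% with normal errors. Switching to the sandwich changed these by only +0.1 to +0.4 point. In a second set (85 infants per arm, unstructured), model-based coverage was 93.0-94.1% with skewed and 93.3-93.6% with normal errors. Non-normality is not what drives the error.

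**4. Unstructured covariance without a small-sample correction.** To first order, with N infants, SE/true SD = 1 - (T-1)/(N-3), and alpha = 2 x [1 - Phi(1.96 x that ratio)]. The last three columns come from complete-data simulations with 4,000 trials per scenario.

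| N | SE/SD | Alpha by formula | Model-based | Sandwich | With correction factor |
|---|---|---|---|---|---|
| 180 | 1 - 7/177 = 0.960 | 6.0% | 5.5% | 5.8% | 4.6% |
| 170 | 1 - 7/167 = 0.958 | 6.0% | 5.6-6.0% | 5.7-6.2% | 4.8-5.1% |
| 140 | 1 - 7/137 = 0.949 | 6.3% | 6.3% | 6.6% | 5.0% |

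The correction factor is sqrt(1 + 2(T-1)/(N-3)): 1.039, 1.041 and 1.050 for N = 180, 170 and 140. It approximates a Kenward-Roger inflation; no full Kenward-Roger fit was run.

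Other runs spread around these values. With 6,000 trials per scenario at 140-180 infants, the model-based error was about 5.5-6.8%, and the factor brought it to 4.5-5.7%. The second set in step 3 was higher: model SE 93-95% of the true SD, error 5.9-7.0% model-based and 6.5-7.3% with the sandwich. One dropout run at 140 infants gave 7.9% and 8.2%. That run probably lies high by chance: the matching run with only 80 infants gave 7.4% model-based, and the Monte Carlo SE is sqrt(0.079 x 0.921/2000) = 0.6 point.

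**5. The procedure as specified, with AIC choosing.** With 170 infants, complete data and the four overall patterns (538-838 trials per structure, Monte Carlo SE about 0.8-1.0 point), the error was 5.2-5.4% model-based and 5.3-5.6% with the sandwich. The result depends on how often AIC picks unstructured. In one exercise that was 41-100% of trials, depending on the scenario.

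**The case against.** A reader might infer that the sandwich fallback itself pushes the nominal 5% tests to 6-7%. The figures do not support that. Nearly all the excess is already in the model-based test when unstructured covariance is fitted, and the switch adds 0.1-0.4 point in most runs at 140-180 infants. The SAP also does not force unstructured covariance: the AIC-selected procedure ran at about 5.2-5.6%.

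It can also be said that the sandwich does widen intervals in the case it is meant for. That stands. Under a too-simple AR(1) pattern it raised the SE by 12-18% and brought the error back to about 5%. The remark in the SAP is therefore true of a misspecified pattern and false as a general property.

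Other points on this side also carry weight. AA and DHA are tested only if the primary comparison succeeds, and a 1% change in an SE alters a decision only at a knife-edge p-value. SAP 6 states an aim, not a coverage guarantee. The SAP's silence on degrees of freedom does not prove that no correction will be used. It does leave the choice open for two confirmatory tests, which a pre-specified plan should not do.

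**Conclusion.** The point holds as a correction to the specification, with small numerical consequences. The trigger is wrong: residual non-normality does not call for a sandwich estimator, and doubt about the covariance does. The stated effect is wrong as a general claim: with an adequate pattern the interval is usually about 1% narrower, and it widens only when the pattern is too simple.

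The larger part is the missing small-sample method. If AIC selects unstructured covariance, SEs are about 4-7% too small and the type I error is roughly 5.5-6.5% at 140-180 infants, with some runs higher. Across AIC-selected patterns it is nearer 5-5.5%. These sizes rest on assumed correlations, dropout and numbers with usable samples, and by-arm versions of the simpler patterns were not simulated.

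It does not follow that the published intervals will be too narrow in every case, or that a clear AA or DHA difference would be lost. A large effect would survive any of these choices.

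**What to change.** In SAP 4.6.2, confirmatory item 1:

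- Delete the normality trigger and the parenthesis on wider intervals. Use residual plots to look for outliers and data errors.
- Keep the AIC selection among the listed patterns. Forcing unstructured covariance is a trade-off and is not needed.
- Specify Kenward-Roger standard errors and degrees of freedom for the AIC-selected model.
- Reserve the sandwich for doubt about the covariance pattern, for instance when a simpler pattern is used because the unstructured fit did not converge. Name the small-sample correction that goes with it.

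Possible wording: *Standard errors and degrees of freedom for the AIC-selected model are computed by the Kenward-Roger method. If the unstructured model does not converge and a simpler pattern is used, a sandwich standard error with a named small-sample correction is reported instead.*

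The cost is two sentences and one option in the SAS code. Intervals become up to about 4-5% wider when unstructured covariance is selected (factors 1.039 to 1.050 above).
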